#### Statistical analysis plan

Data will be analysed with the help of a trial statistician. Data will be analysed using SPSS for windows 17.0 (IBM, NY, USA). A detailed analysis plan will be developed during the trial prior to commencement of analysis. In brief, for continuously distributed data, differences between groups will be tested using independent samples *t*-tests with transformations of variables to normality if appropriate or non-parametric equivalents. Chi-squared tests (or Fishers Exact tests) will be used for categorical variables. A *P* value of 0.05 will be considered as significant. We will test for significant correlations between changes in the biological markers using standard methods. The treatment effect will be analysed on an intention-to-treat basis. For the further examination of relationships between a binary variable and known explanatory variables, the following tests will be applied as appropriate. Logistic regression will be used to provide the estimated risk ratios for the treatment effect with associated 95% confidence intervals. Time to event outcomes such as duration of ventilation or duration of hospital stay will be analysed by survival methods and reported as hazard ratios and 95% confidence intervals. A single final analysis is planned at the end of the trial.

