### Community-acquired pneumonia-associated sepsis and neutrophil extracellular traps

During the early stages of CAP-associated sepsis, NET production is suppressed with improvements occurring during resolution. In addition, NET release was significantly lower in CAP patients who meet the criteria for severe sepsis. Taken together these data suggest that neutrophil function is a feature of CAP-associated sepsis, especially in the elderly, and that statin therapy may have potential to restore the defects in these neutrophils both *in vivo* and *in vitro*.

In light of these data, we hypothesise that the increased incidence and poorer outcomes observed in the elderly population in relation to pneumonia and sepsis may be due to defective neutrophil function, and that restoration of these functions may therefore improve outcome, especially in the elderly. The SNOOPI trial therefore aims to determine whether oral treatment with simvastatin optimises neutrophil anti-microbial functions in elderly patients admitted into Queen Elizabeth Hospital Birmingham (QEHB) with septic pneumonia, improving patient outcomes in the elderly. Alterations in neutrophil function will be related to clinical outcome, disease-relevant severity scores and biomarkers present in blood and urine.

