### Outcome measures

#### Primary outcome

The primary outcome will be NET production within 72 to 96 hours of treatment with simvastatin or placebo, measured in response to a number of inflammatory mediators including IL8, fMLP and LPS and using phorbol-12-myristate-13-acetate as a positive control
[18] (for full methods, see Additional file
1).

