#### Secondary outcomes

Secondary outcomes of this trial include parameters describing neutrophil migratory capacity; ROS production; neutrophil phagocytic capacity; safety and tolerability of simvastatin administration within this patient group; biological markers of neutrophil activation (for example, myeloperoxidase), the inflammatory response (for example, IL6), alveolar epithelial and endothelial injury (for example, von Willebrand factor), and systemic endothelial function biomarkers (for example, albumin:creatinine ratio); pulmonary extracellular matrix (ECM) degradation and turnover of peptide; and, finally, the relationship of baseline and changes in parameters described above to clinical relevant outcomes (survival, development of organ failure, admission onto intensive therapy unit, sequential organ failure assessment score, ventilator-free days and muscle wastage during the inpatient stay). These assessments will be made at baseline, on days 4 and 7, and in convalescent samples.

Neutrophil migratory capacity will be measured using a modified Dunn chamber as described previously
[15, 19]; neutrophil ROS production will be measured using a luminol-based assay and phagocytic capacity measured by flow cytometry. Plasma indices of neutrophil activation, the inflammatory response and alveolar epithelial and endothelial injury will be measured by enzyme-linked immunosorbent assay, and systemic endothelial function biomarkers and pulmonary ECM degradation will be measured in urine collected from an indwelling urinary catheter (for full methods, see Additional file
1). These assessments will be made at baseline, on days 4 and 7, and in convalescent samples (≥6 weeks post-discharge).

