### Power and sample size estimate

Mean NET production in CAP-associated sepsis patients is suppressed down to 7,500 arbitrary units (AU) versus 13,200 (SD 2,432) AU in age-matched control neutrophils. At day 4, levels remain suppressed at 8,200 AU (SD 5,100) but, by day 7, patient neutrophils have increased baseline NET production almost back to normal (11,500 AU (SD 6,100), *P* = 0.9) versus normal matched controls. If we assume that statin treatment *in vivo* has a similar magnitude of effect as it does *in vitro* on elderly patient neutrophils (+80% NET production), then 18 patients in each arm would be needed to increase NET production by 5,000 AU from day 0 to day 4 with a power of 0.8, *P* = 0.05. For 90% power we would need 23 patients in each arm. To allow for drop outs due to death and so forth, we intend to recruit 30 patients in each arm. Based on our other preliminary data with 23 patients completing each arm, we would have an 80% power to detect significant increases in both chemotactic velocity (effect size +0.5, ±35%) and ROS production (effect size ±57%). For *in vitro* work on healthy elderly patient neutrophils we typically require 6 to 8 patient samples for mechanistic studies so these patient numbers should be adequate for additional mechanistic work.

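### The only between-group test named for continuous outcomes is an unadjusted t-test; making baseline-adjusted ANCOVA the primary analysis of NET production would add precision and protect against chance imbalance

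*Protocol article*

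**What the plan says.** Under Primary outcome: "The primary outcome will be NET production within 72 to 96 hours of treatment with simvastatin or placebo". This is worded as a level, not as a change.

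Under Statistical analysis plan, for continuous data, "differences between groups will be tested using independent samples" t-tests. The sentence goes on to allow variables to be transformed, or a non-parametric equivalent to be used. No baseline covariate is mentioned for the treatment comparison. The section also says: "A detailed analysis plan will be developed during the trial prior to commencement of analysis".

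Under Power and sample size estimate, the target is to "increase NET production by 5,000 AU from day 0 to day 4", which needs a day-0 NET value. The spread comes from day-4 levels: "At day 4, levels remain suppressed at 8,200 AU (SD 5,100".

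Under Secondary outcomes: "These assessments will be made at baseline, on days 4 and 7, and in convalescent samples (≥6 weeks post-discharge". NET production is not itself in that list, so a baseline NET sample is inferred from the sample-size text and this schedule together.

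**The concern.** If a day-0 NET value is collected, a two-sample comparison of day-4 levels leaves it unused. Part of the variation in day-4 NET production between patients is likely to be present already at entry, and adjusting for baseline removes that part from the standard error. In a trial this small, the arms can also differ by chance at baseline by an amount that matters beside the target effect. The unadjusted estimate carries that difference through in proportion to the correlation between baseline and outcome.

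The article gives a reason to expect such variation: it reports that "NET release was significantly lower in CAP patients who meet the criteria for severe sepsis". It gives no size for that difference. At stake are the precision of the primary estimate and how much it depends on the luck of allocation.

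**Working it through.** **Inputs from the article.** SD of day-4 NET 5,100 AU; target 5,000 AU; significance level 0.05 (sidedness not stated, taken as two-sided); 18 per arm for 80% power, 23 for 90%; 30 per arm recruited. Untreated means: 7,500 AU initially, 8,200 AU at day 4.

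**Assumptions.** The correlation ρ between baseline and day-4 NET is not given; the range shown is 0.3 to 0.7. The SD at baseline in patients is not given; where needed it is set equal to the day-4 SD.

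**1. The article's own figures.** A two-sample t-test with standardised effect 5,000 / 5,100 = 0.980, two-sided 0.05, needs 17.35 per arm for 80% power and 22.87 for 90%. Rounded up, these are 18 and 23, an exact match. The trial was therefore sized as an unadjusted comparison using the spread of day-4 levels.

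**2. Effect of baseline adjustment.** ANCOVA has residual SD = 5,100 × √(1 − ρ²) and 2n − 3 degrees of freedom. For ρ = 0.3, 0.5 and 0.7, the residual SD is 4,865, 4,417 and 3,642 AU, and the variance falls by 9%, 25% and 51%.

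Power by non-central t with 23 per arm:

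| Between-group difference | Unadjusted | ρ = 0.3 | ρ = 0.5 | ρ = 0.7 |
|---|---|---|---|---|
| 5,000 AU | 90.2% | 92.6% | 96.3% | 99.5% |
| 4,300 AU | 79.9% | 83.4% | 89.7% | 97.5% |

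The second row reads the target literally as a rise within the treated arm: 7,500 + 5,000 = 12,500 AU, against 8,200 AU untreated at day 4, so 12,500 − 8,200 = 4,300 AU. The article does not say which reading is meant.

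With 30 per arm and 5,000 AU, power is 96.2% unadjusted and 97.5%, 99.1% and 99.9% adjusted.

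**3. Chance imbalance.** The standard error of the baseline difference, in SD units, is √(2/n). With n = 30 it is 0.258, so the 95% range is ±1.96 × 0.258 = ±0.51 SD. With n = 23 it is ±0.58 SD. With equal SDs, an imbalance at the limit for 30 per arm shifts the unadjusted estimate by ρ × 0.506 × 5,100: about 770, 1,290 or 1,810 AU for ρ = 0.3, 0.5 or 0.7.

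**4. Cost.** At ρ = 0 and 23 per arm, the lost degree of freedom takes less than 0.1 percentage point of power. Estimating the covariate effect inflates the variance by an expected (2n − 3)/(2n − 4) = 43/42 = 1.024. The two balance when (1 − ρ²) × (2n − 3)/(2n − 4) = 1, that is ρ = √(1/(2n − 3)) = √(1/43) = 0.15. The break-even is 0.17 with 18 per arm and 0.13 with 30.

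**5. If the t-test were on change from day 0.** With equal SDs, the SD of change is 5,100 × √(2(1 − ρ)). At 5,000 AU and 23 per arm, power is 78.5% at ρ = 0.3 (SD 6,034). It equals the unadjusted 90.2% at ρ = 0.5. ANCOVA gives 92.6% and 96.3% at the same two values.

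**The case against.** The strongest reply is that the t-test is a generic rule given in brief, that a detailed plan is promised before analysis, and that nothing excludes baseline adjustment there. This stands in part: the article does not tie the test to the primary outcome by name, and covariates are often left to the later plan. But the point concerns the method that is stated. It is the only one given for comparing continuous data between arms, and it is the one on which the sample size was calculated. A detailed plan that simply expanded it would keep the less efficient test.

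Several stronger readings are tempting and are not supported.

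- *The unadjusted test is wrong.* It is not. In a randomised comparison its error rate and confidence interval already allow for chance imbalance.
- *The trial is underpowered without adjustment.* On a 5,000 AU between-group difference, the unadjusted test already has 90% power with 23 per arm and 96% with 30.
- *Baseline NET is measured in every patient, or the plan certainly ignores it.* The article states neither. It also leaves open whether the t-test is on the level or on the change, and a change score would use baseline, though less efficiently than ANCOVA.
- *NET production depends strongly on severity.* The article reports a significant difference without its size.
- *The plan overlooks skewness.* It allows transformation and non-parametric tests.
- *Adjustment costs nothing.* It costs slightly more than nothing, and below a correlation of about 0.15 it brings no net gain.

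**Conclusion.** The point holds as a recommendation to improve precision; it does not correct an error. With 23 per arm, the gain is about 2 to 9 percentage points of power if the between-group difference is 5,000 AU, and about 4 to 18 points if it is 4,300 AU. Both ranges assume a correlation of 0.3 to 0.7, and the article gives none. Adjustment would also remove most of the effect of a chance baseline imbalance on the estimate. At the edge of its 95% range with 30 per arm, that imbalance could move the unadjusted result by roughly 770 to 1,810 AU, under the further assumption of equal SDs.

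All these figures are for raw arbitrary units and a single covariate. The gain on a log scale was not calculated. Adjusting for severe sepsis at entry, and mixed models for the other outcomes, are options that this point does not rest on.

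**What to change.** In the analysis section, or in the detailed plan before analysis begins, name the primary analysis as an ANCOVA of NET production at 72 to 96 hours on treatment arm with day-0 NET production as covariate. Put both NET values on the same scale: log if the transformation that the plan already allows proves necessary, otherwise raw units. State that NET production is measured at day 0, and say how a missing baseline value is handled. Keep the independent-samples t-test or its rank equivalent as a sensitivity analysis.

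The cost is wording and one degree of freedom. If day-0 NET is sampled as the sample-size text implies, no further patients or samples are needed.

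### Logistic regression is named as the source of risk ratios for binary variables, but its coefficient gives an odds ratio and no conversion is stated

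*Protocol article*

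**What the plan says.** The Statistical analysis plan section of the protocol article assigns t-tests or non-parametric equivalents to continuous data, and chi-squared or Fisher's exact tests to categorical variables. It then adds a further layer: "For the further examination of relationships between a binary variable and known explanatory variables, the following tests will be applied as appropriate". The next sentence fixes both model and measure: "Logistic regression will be used to provide the estimated risk ratios for the treatment effect with associated 95% confidence intervals". Time-to-event outcomes are paired with hazard ratios. Odds ratios are not mentioned anywhere in the article, and neither is a log link, a log-binomial model, a modified Poisson model or standardisation of model predictions. The section also promises more detail: "A detailed analysis plan will be developed during the trial prior to commencement of analysis".

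The binary variables most likely to be meant stand in the Secondary outcomes section: "survival, development of organ failure, admission onto intensive therapy unit". That section presents them, with other items, as clinical outcomes to which the neutrophil and biomarker measurements will be related. It gives no expected event rate for any of them.

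The primary outcome is a continuous laboratory measure: "The primary outcome will be NET production within 72 to 96 hours of treatment with simvastatin or placebo".

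**The concern.** A logistic model is linear in the log odds, so exponentiating its treatment coefficient gives a ratio of odds. A risk ratio is a different quantity. The two agree at the null, nearly agree when events are rare, and diverge as events become common, with the odds ratio always further from 1. A reader told that a figure is a risk ratio will take 0.375 to mean a 62.5% reduction in risk, when the risks behind it may show only a 50% reduction.

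This is more than a detail left for later. The sentence already commits to a model and a measure, and the two do not fit together. If the analyst follows it literally, the estimate and the interval limits carry the wrong label. If the analyst notices the mismatch only at analysis, the choice of effect measure is made after the data are available.

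**Working it through.** **1. The plan's own reproducible figure, to see whether it is touched.** Inputs from Power and sample size estimate: a difference of 5,000 AU, SD 5,100 AU ("At day 4, levels remain suppressed at 8,200 AU (SD 5,100"), power 0.8, and significance level 0.05 ("value of 0.05 will be considered as significant"). A two-sided independent-samples t-test with standardised effect 5,000/5,100 = 0.980 needs 17.35 per arm, rounded up to 18. This matches "then 18 patients in each arm would be needed to increase NET production by 5,000 AU from day 0 to day 4". At 90% power it needs 22.87, rounded up to 23, which is also the stated figure. The calculation uses means and an SD of NET production only. No binary outcome or logistic model enters it, so the point below leaves it intact.

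**2. Relation between the two measures.** Let p0 be the control risk and p1 the simvastatin risk.

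- Risk ratio: RR = p1/p0
- Odds ratio: OR = [p1/(1 − p1)] / [p0/(1 − p0)] = RR × (1 − p0)/(1 − p1)

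If p1 < p0, the factor (1 − p0)/(1 − p1) is below 1, so OR < RR < 1. If p1 > p0, the factor is above 1, so OR > RR > 1. If p1 = p0, both equal 1.

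Example: p0 = 0.40 and RR = 0.50 give p1 = 0.20. Then OR = (0.20/0.80)/(0.40/0.60) = 0.250/0.667 = 0.375.

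**3. Size over a range.** The article gives no event rates, so every control risk and every true RR here is an assumption.

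| Assumed control risk | OR if true RR = 0.50 | OR if true RR = 0.80 | OR if true RR = 1.50 |
|---|---|---|---|
| 1% | 0.497 | 0.798 | 1.508 |
| 10% | 0.474 | 0.783 | 1.588 |
| 20% | 0.444 | 0.762 | 1.714 |
| 30% | 0.412 | 0.737 | 1.909 |
| 40% | 0.375 | 0.706 | 2.250 |
| 50% | 0.333 | 0.667 | 3.000 |

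At 1% control risk the label hardly matters. At 40%, a true halving of risk would be printed as a 62.5% reduction.

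**4. The interval.** Take hypothetical counts at the planned 30 per arm: 6/30 events on simvastatin and 12/30 on placebo.

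- Logistic regression: OR = (6/24)/(12/18) = 0.375. SE of log OR = √(1/6 + 1/24 + 1/12 + 1/18) = 0.589. 95% CI 0.118 to 1.190.
- Poisson model with robust variance: RR = (6/30)/(12/30) = 0.500. SE of log RR = √(1/6 − 1/30 + 1/12 − 1/30) = 0.428. 95% CI 0.216 to 1.157.

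The estimate and both limits of the odds ratio lie further from 1 than those of the risk ratio.

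**5. Can a logistic model give a risk ratio at all?** Yes, with one more step. Predicting each patient's risk under each arm from the same fitted model and averaging gives 0.20 and 0.40, a ratio of 0.500. The article does not state this step.

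**The case against.** The strongest reply is that the sentence is loose wording with little consequence. Much of that stands. The categorical comparisons use chi-squared or Fisher's exact tests. Logistic regression enters only for further examination, where appropriate. A wrong label changes neither those tests nor the logistic model's own test of no treatment effect. Because standardised predictions from a logistic model give a valid risk ratio, the sentence could be honoured in a correct way, and the promised detailed plan could say so. The overstatement is therefore conditional on the raw coefficient being reported as a risk ratio.

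What does not stand is that the promised plan turns the sentence into a mere omission. The text states a pairing that is wrong without an extra step, and it names no such step.

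A reader might infer three stronger claims, none of which the document supports.

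- *Every binary treatment effect will be exaggerated.* The scope of the logistic model is limited, as above, and at the null the two measures coincide. The Secondary outcomes section lists survival, organ failure and intensive therapy admission as outcomes to be related to laboratory parameters, not plainly as endpoints compared between arms. The phrase about the treatment effect in the Statistical analysis plan section makes a between-arm use possible, but does not establish it for these three.
- *Events must be common here, so the distortion must be large.* Older patients with sepsis, some identified in intensive care, make this plausible, as does the rise from 23 to 30 per arm. But that allowance of 7 in 30 (23%) pools death with other reasons for loss, and the article gives no rate for any binary outcome.
- *The trial's main result is at risk.* NET production is continuous and is not analysed by this model.

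**Conclusion.** The point holds as a mismatch between model and effect measure. Its practical effect is conditional: an overstated effect follows only if the exponentiated coefficient and its interval are presented as a risk ratio. Its size rests wholly on assumed event rates, running from negligible at 1% control risk (0.497 for a true 0.50) to material at 40% (0.375 for a true 0.50). It is confined to binary secondary or exploratory analyses. Severity is minor to moderate.

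**What to change.** Amend the one sentence in the Statistical analysis plan section, and carry the same wording into the detailed plan before analysis starts. Either option is enough:

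- keep logistic regression and call the estimate an odds ratio with its 95% confidence interval; or
- keep the risk ratio as the measure and name a method that yields it with a matching interval: modified Poisson regression with robust variance, log-binomial regression, or marginal standardisation of the logistic model.

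The cost is one sentence and standard software. No data collection, sample size or primary analysis changes.

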#### Trial organisation/oversight

Trial oversight will be provided by a Trial Steering Committee comprising investigators, clinicians and trialists. An independent data monitoring committee will monitor the safety of participants enrolled in the trial through regular review of adverse event reports. An interim analysis of efficacy is not planned.

## Discussion

Preliminary data on which this study is based suggests a significant role of neutrophil immune-paralysis in the development and progression of sepsis, a process that may be amenable to correction by simvastatin. This study will investigate the ability of *in vivo* simvastatin therapy to modulate neutrophil anti-microbial functions in CAP-associated sepsis and ultimately improve patient outcomes.

## Trial status

Patient recruitment commenced in December 2013 and is expected to continue for 18 months with patient recruitment ending in April 2015.

## Abbreviations

ALI: acute lung injury
CAP: community-acquired pneumonia
ECM: extracellular matrix
fMLP: f-Met-Leu-Phe
IL: interleukin
IMP: investigational medicinal product
LPS: lipopolysaccharide
MODS: multi-organ dysfunction
NET: neutrophil extracellular trap
QEHB: Queen Elizabeth Hospital Birmingham
ROS: reactive oxygen species
SIRS: systemic inflammatory response syndrome.
